### Exclusion Criteria:

- Not willing to participate
- Unable to give samples for follow up
- Severe intercurrent medical condition
- Diarrhoea at first sampling

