## **Efficacy study**

### Experimental design

Following obtaining informed consent, schoolchildren in the target age range group will be recruited and asked to provide a recent stool sample (an interval of less than 4 hours) that will be processed to determine the FEC for each STH present. A small subsample of faecal samples will be also collected for coproculture to identify the hookworms species present and preserve parasite material for subsequent analysis (Annex 2.3).

All children providing stool samples will be treated with Albendazole (GSK®) single tablet of 400mg under supervision (chewing + water). The Albendazole will be provided (free) by the coordinating group.

14 to 30 days after treatment a second faecal sample will be collected from the children to determine again FEC. Only children infected with a minimum of 150 eggs/gram of any species of STH (i.e. *Ascaris* or hookworms or *Trichuris*) at the first sampling should be included in the second sampling. However, for the other STH present FEC should also be determined at the second sampling.

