### Data analysis

Both CR and ERR will be considered to monitor to efficacy.

To avoid distortion due to the density dependant effect, the CR and ERR will be also calculated separately in the different classes of intensity at baseline.

---

 Statistical power analyses, based on random simulations of correlated overdispersed FEC data reflecting the variance-covariance structure in a selection of real FEC data sets, suggest that a sample size of up to 200 individuals ( $\alpha = 0.05$ , power = 80%) is required to detect a 10 percentage point drop from a null efficacy of  $\sim 80\%$  (mean percentage FEC  $\Delta$  per individual) over a wide range of infection scenarios. Standard power analyses for proportions also indicate that the detection of a  $\sim 10$  percentage point drop from a null cure rate requires sample sizes ranging up to 200 (the largest samples being required to detect departures from null efficacies around 50%). Given an anticipated non-compliance rate of 25%, a sample of 250 individuals with  $>250$  egg/g pre-treatment should therefore be followed up for post-treatment FEC data at each study locality.

The following indexes should be used to monitor drug efficacy:

Cure rate

$$[N \text{ egg positive post-treatment} / N \text{ egg positive pre-treatment}] * 100$$

Mean FEC  $\Delta$  per individual

$$\frac{\sum_{i=1}^{i=N} [T1_i - T2_i]}{N}$$

Where T1 = pre-treatment FEC, T2 = post-treatment FEC, and  $i$  = the  $i$ th subject.

Mean percentage FEC  $\Delta$  per individual

$$\frac{\sum_{i=1}^{i=N} \{ [T1_i - T2_i] / T1_i \} * 100}{N}$$

Percentage  $\Delta$  in the sample mean FEC

$$\{ [\text{sample mean T1} - \text{sample mean T2}] / \text{sample mean T1} \} * 100$$

Confidence intervals for these indexes can be generated by a standard method for proportions in the case of cure rate (the exact binomial method) and by bootstrap resampling methodologies for the FEC  $\Delta$  indexes.

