### Procedure

1. Weigh 2 grams of faeces in a plastic beaker (100 ml).
2. Add 30 ml of the flotation fluid saturated salt solution,
3. Homogenise and pour the faecal suspension 3 times through a tea strainer to withhold the large debris.
4. Homogenise the filtrate by pouring it at least 5 times from one beaker to another and fill up one side of a regular McMaster counting chamber by using a pasteur pipette. Repeat for the other side.
5. Allow the counting chamber to stand for 2 minutes, place under a light microscope and examine using a 100x magnification. All the eggs under the two separate grids are counted (this represents a volume of  $2 \times 0.15$  ml)
6. The number of eggs per gram of faeces is obtained by multiplying the total number of eggs under the two grids by 50. The sensitivity of the test is 50.

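### Diarrhoea is screened out only at the first sampling, so a diluted stool can lower the post-treatment egg count but not the baseline count, a small bias towards higher apparent efficacy

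*Protocol*

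**What the plan says.** The Exclusion Criteria of the efficacy study include "Diarrhoea at first sampling". The criterion names the first sampling expressly, and no other section, Annex 2 included, sets a consistency condition for the second stool.

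The Experimental design section says of recruitment that children are "asked to provide a recent stool sample (an interval of less than 4 hours"). The sentence on follow-up reads "14 to 30 days after treatment a second faecal sample will be collected from the children to determine again FEC". Entry to the second sampling depends on the baseline count alone: "Only children infected with a minimum of 150 eggs/gram of any species of STH".

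The Data analysis section builds its egg-count indexes from the two counts: "Where T1 = pre-treatment FEC, T2 = post-treatment FEC". It gives no adjustment for stool condition. Every child who provides a stool is treated, so there is no untreated comparison.

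Annex 2.1 fixes the unit of measurement: "Weigh 2 grams of faeces in a plastic beaker (100 ml"), suspended in 30 ml of flotation fluid, with the result obtained by "multiplying the total number of eggs under the two grids by 50. The sensitivity of the test is 50".

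**The concern.** A before-after comparison is fair only if both measurements are taken under like conditions. Here a condition that affects the measurement is controlled on one side only. If egg output is unchanged, extra water in the stool means fewer eggs in the 2 g weighed out. At baseline such stools are removed. At follow-up they are counted, they lower T2, and the fall is read as drug effect. Nothing on the T1 side offsets it, and no untreated group would reveal it.

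The direction matters because the trial is meant to validate a standard method for monitoring efficacy, and its power statement concerns finding a fall in efficacy. A bias that makes efficacy look higher works against that aim and would pass to later users of the method. Secondary objective 1 also asks for an analysis that deals with confounding factors. Stool consistency is a candidate, yet the protocol does not require it to be recorded, and no later analysis can adjust for it if it is not.

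**Working it through.** **Unit of measurement (Annex 2.1).** Inputs: 2 g of faeces, 30 ml of fluid, 2 × 0.15 ml = 0.3 ml read. Conversion factor = 30 / (2 × 0.3) = 50, which reproduces the protocol's multiplier. The 2 g is wet weight, so the count depends on water content, and one egg seen corresponds to 50 eggs per gram.

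**Yardstick (footnote 1).** The sample size "is required to detect a 10 percentage point drop from a null efficacy of" about 80%. A bias can therefore be judged against a fall from 80% to 70%.

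**Effect on ERR.** Let f be the share of follow-up stools that are loose and l the fractional loss of eggs per gram in them, with looseness unrelated to egg output. Then:

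recorded ERR = 1 − (1 − true ERR)(1 − f × l)

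The documents give neither f nor l. Both are assumptions, and the working range is f = 2% to 10% with l = 50%.

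| f | l | f × l | True ERR 70% | True ERR 80% |
|---|---|---|---|---|
| 2% | 50% | 1% | 70.3% | 80.2% |
| 5% | 50% | 2.5% | 70.75% | 80.5% |
| 10% | 50% | 5% | 71.5% | 81.0% |
| 30% | 75% | 22.5% | 76.75% | 84.5% |

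Within the working range the bias is 0.2 to 1.5 points. The last row is a deliberately severe case and gives 4.5 to 6.75 points, still short of 10.

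**What would hide the whole design effect.** For a true 70% to be recorded as 80%: 0.30 × (1 − x) = 0.20, so x = 1/3. One third of all follow-up eggs per gram would have to be lost. At half dilution, that means f = (1/3) / 0.5 = 67% of follow-up stools being loose.

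**A single child.** A true reduction of 70% with a follow-up stool diluted by half is recorded as 1 − 0.30 × 0.5 = 85%. The distortion is large for that child and small in the group because few children are affected.

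**Effect on apparent cure.** Assuming Poisson counts, the probability that a child still shedding E eggs per gram is read as negative is exp(−E(1 − l)/50).

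| E (eggs/g) | Undiluted | Diluted by half |
|---|---|---|
| 50 | 0.368 | 0.607 |
| 100 | 0.135 | 0.368 |

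Among children still shedding 100 eggs per gram, the share read as negative rises by f × (0.368 − 0.135): 0.5 points at f = 2% and 2.3 points at f = 10%. Cure is meant here in its ordinary sense, negative after treatment.

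**The case against.** **Eligibility criteria apply at enrolment.** A child already enrolled and treated cannot be made ineligible by a later loose stool, so the wording may simply reflect where the criterion sits. That explains the asymmetry but does not remove it, since no sampling instruction covers the second stool either. Analysis-set rules can be left to a statistical analysis plan. Collecting a repeat stool and recording consistency cannot, because they must happen in the field.

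**The effect is small.** This stands. One might infer that the gap could erase the whole 10-point drop, but that needs about two thirds of follow-up stools to be loose at half dilution, and nothing in the documents suggests this.

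**Stool age.** A reader might also infer that the 4-hour interval binds only the first sample, that aged stools are accepted after treatment, and that every such fault favours the drug. The documents do not support this. The interval is stated once, in the recruitment sentence, and the instruction to determine the count again can be read as repeating the same procedure. No section says that eggs are lost as stool ages. The Kato-Katz annex notes that hookworm eggs clear on the prepared slide, which is a different matter, and McMaster is the standard method. Only dilution has a direction that can be derived from the documents.

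**Dropping loose follow-up samples has its own cost.** This also stands. Excluding children for a post-treatment event can introduce selection. It would also reduce numbers: 250 less 25% non-compliance is 250 × 0.75 = 187.5, already below the 200 named in footnote 1.

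**Conclusion.** The point holds for diarrhoea. The criterion is expressly one-sided, the count is per gram of wet stool, and efficacy is taken straight from the two counts, so dilution at follow-up pushes ERR and the apparent proportion cured upwards. With 2% to 10% of follow-up stools loose and diluted by half, the ERR bias is about 0.2 to 1.5 points at true ERR 70% to 80%. It is a minor bias of known direction, well inside the 10-point design effect.

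This rests on three assumptions that the documents do not supply: the frequency of loose follow-up stools, the degree of dilution, and no link between looseness and egg output. The figures for apparent cure also assume Poisson counts. For the 4-hour interval, the only conclusion is that the text should say it covers both samples.

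**What to change.** In Experimental design and Exclusion Criteria:

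- State that the stool-consistency condition applies to the second sample as well as the first.
- If the follow-up stool is diarrhoeal, collect a repeat within the existing 14 to 30 day window.
- If no repeat is obtained, keep the sample in the primary analysis, flag it, and report cure rate and ERR with and without flagged samples.
- Record stool consistency and time to processing at both visits.
- Say that the under-4-hour interval covers both samples, as a clarification.

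The cost is two or three fields on the form and occasional re-collection inside a window that already exists. The primary analysis loses no children. The stool data have to be planned before sampling, since they cannot be recovered afterwards.

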### Data analysis

Both CR and ERR will be considered to monitor to efficacy.

To avoid distortion due to the density dependant effect, the CR and ERR will be also calculated separately in the different classes of intensity at baseline.

---

 Statistical power analyses, based on random simulations of correlated overdispersed FEC data reflecting the variance-covariance structure in a selection of real FEC data sets, suggest that a sample size of up to 200 individuals ( $\alpha = 0.05$ , power = 80%) is required to detect a 10 percentage point drop from a null efficacy of  $\sim 80\%$  (mean percentage FEC  $\Delta$  per individual) over a wide range of infection scenarios. Standard power analyses for proportions also indicate that the detection of a  $\sim 10$  percentage point drop from a null cure rate requires sample sizes ranging up to 200 (the largest samples being required to detect departures from null efficacies around 50%). Given an anticipated non-compliance rate of 25%, a sample of 250 individuals with  $>250$  egg/g pre-treatment should therefore be followed up for post-treatment FEC data at each study locality.

The following indexes should be used to monitor drug efficacy:

Cure rate

$$[N \text{ egg positive post-treatment} / N \text{ egg positive pre-treatment}] * 100$$

Mean FEC  $\Delta$  per individual

$$\frac{\sum_{i=1}^{i=N} [T1_i - T2_i]}{N}$$

Where T1 = pre-treatment FEC, T2 = post-treatment FEC, and  $i$  = the  $i$ th subject.

Mean percentage FEC  $\Delta$  per individual

$$\frac{\sum_{i=1}^{i=N} \{ [T1_i - T2_i] / T1_i \} * 100}{N}$$

Percentage  $\Delta$  in the sample mean FEC

$$\{ [\text{sample mean T1} - \text{sample mean T2}] / \text{sample mean T1} \} * 100$$

Confidence intervals for these indexes can be generated by a standard method for proportions in the case of cure rate (the exact binomial method) and by bootstrap resampling methodologies for the FEC  $\Delta$  indexes.

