## **Objectives**

### **Overall Objective**

The overall objective is to develop and validate a standard protocol to monitor efficacy of anthelmintics of Soil Transmitted Helminths (STH) in populations with different exposure to anthelmintics.

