### **Parasitological technique to determine FEC**

The standard coprological technique to be used will be the McMaster method, a user-friendly method widely practiced in Veterinary Medicine. The McMaster method is a quantitative method for analysis of FEC. For each sample one chamber (two compartments) will be counted (sensitivity of 50 eggs/gram) (Annex 2.1). A video showing the McMaster technique will be made and provided to all participating laboratories.

McMaster slides will be provided free by the coordinating group

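### Intensity classes can only be formed from the same single count that serves as T1, so class-specific ERRs carry a regression-to-the-mean gradient and should be labelled descriptive

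*Protocol*

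**What the plan says.** The Data analysis section gives cure rate (CR) and ERR as the efficacy measures and adds a stratified version. Its purpose is "To avoid distortion due to the density dependant effect", and its method is that "the CR and ERR will be also calculated separately in the different classes of intensity at baseline". Class limits and the classifying count are not stated.

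The reduction indexes are printed below that, with "Where T1 = pre-treatment FEC, T2 = post-treatment FEC".

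The baseline measure is set elsewhere. Under Experimental design, each child is "asked to provide a recent stool sample (an interval of less than 4 hours) that will be processed to determine the FEC". Under Parasitological technique to determine FEC, "For each sample one chamber (two compartments) will be counted (sensitivity of 50 eggs/gram"; Annex 2.1 multiplies the eggs seen by 50. The two-chamber count belongs to the preliminary comparison of techniques only. Children need at least 150 eggs per gram (epg), that is three eggs seen, on this baseline count to enter the second sampling.

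The overall objective is a standard monitoring protocol for "populations with different exposure to anthelmintics", and the Sample size section lets sites include one group with and one without mass drug administration.

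**The concern.** One count does three jobs: it decides entry, it is the only baseline value from which a class can be formed, and it is the baseline term of the ERR. Any chance error in it moves the child between classes and moves the child's apparent reduction in the same direction. A child whose count happened to be low lands in a lighter class with too small a denominator, so the ERR there is too low. A child whose count happened to be high does the reverse. The result is an ERR that rises from light to heavy with no such pattern in the drug's effect.

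Three wrong conclusions become possible. A uniformly effective drug may look weaker in light infections. A real fall of efficacy with intensity may be flattened. And two areas with the same efficacy but different intensity distributions may show different ERRs in the same class. Bootstrap intervals describe sampling variation around the biased value and do not remove the bias. No choice of class limits removes it either, because there is no second baseline count.

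**Working it through.** **The plan's own figure.** The footnote to Sample size gives up to 200 children for a drop of about 10 points in cure rate. A two-sided one-sample test of 50% against 40% (alpha 0.05, power 80%) gives n = [1.96 × √(0.5 × 0.5) + 0.842 × √(0.4 × 0.6)]² / 0.10² = 194, which agrees. The parallel simulation for egg counts cannot be reproduced, because its variance-covariance inputs are not given.

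**From the protocol.** One count at 50 epg per egg; entry at three eggs or more; T1 in the denominator; reference efficacy about 80%.

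**Assumed, because the protocol does not give them.** True intensity gamma with shape k = 0.5 and mean 500 or 1500 epg; sample-to-sample CV from 0 to 0.71; classes 150-499, 500-999, 1000-1999, 2000-4999 and 5000+ epg; a true reduction of 80% in every child. ERR here means the percentage change in sample means.

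**Counting error only, exact.** With y eggs seen, the expected true FEC is 50(y + k)/(1 + 50k/m), where m is the mean. At y = 3 (150 epg):
- m = 500: 50 × 3.5/1.05 = 166.7; expected T2 = 0.2 × 166.7 = 33.3; ERR = 1 − 33.3/150 = 77.8%.
- m = 1500: 50 × 3.5/1.0167 = 172.1; expected T2 = 34.4; ERR = 1 − 34.4/150 = 77.1%.

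So even at the entry threshold, counting error alone costs only 2-3 points.

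**With sample-to-sample variation.** Simulation of 1.5 million children per scenario: T1 = 50 × Poisson(λf₁/50), T2 = 50 × Poisson(0.2λf₂/50), where λ is true intensity and f₁, f₂ are independent gamma factors with mean 1 and the stated CV; children with T1 ≥ 150 are kept. ERR (%), lightest to heaviest class:

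| CV | Mean 500 epg | Mean 1500 epg | All children |
|---|---|---|---|
| 0 | 79-80-81-81-81 | 79-80-80-80-80 | 80.1-80.4 |
| 0.25 | 78-79-81-82-84 | 77-78-79-80-82 | 80.1-80.4 |
| 0.5 | 73-78-81-85-88 | 69-73-76-79-85 | 80.2-80.8 |
| 0.71 | 68-77-82-87-91 | 56-67-73-80-87 | 80.4-81.5 |

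The all-children value barely moves, so the gradient comes from the classing and not from the 150 epg entry rule. Tertile classes, other values of k and a lognormal population give the same pattern: over means of 300-3000 epg at CV 0.5, the light tertile reads about 67-77%.

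**Between areas.** In the lightest class the two areas differ by 73 − 69 = 4 points at CV 0.5 and 68 − 56 = 12 points at CV 0.71, with identical efficacy.

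**Masking.** If true efficacy is 90% below 500 epg, 80% from 500 to 2000 and 70% above (mean 500, CV 0.5), T1 classes read 80-79-79-80-83%. The real decline disappears.

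**Higher efficacy.** At a true 95% and CV 0.5, the lightest class reads 92-93%.

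**The case against.** The strongest objection concerns size. The only noise the protocol fixes is the 50 epg counting unit, and with that alone the lightest class is about one point low. A shortfall near 10 points needs an assumed CV of about 0.5 or more. It also needs a narrow light class: at CV 0.5, a class of 150-4999 epg reads 80% (mean 500) or 77% (mean 1500). All this stands, so the size can be given only as a range.

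A reader might infer that the study will show a false drop of the size it was planned to find, since the footnote speaks of power to "detect a 10 percentage point drop from a null efficacy of" about 80%. The documents do not support that. That target belongs to the mean of individual percentage changes in a whole sample, not to a group-mean ERR within a class. The statement that the all-children result stays near 80-81% likewise applies only to the ERR of sample means: the individual-percentage index itself reads about 74.5-76.5% overall at CV 0.5.

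A reader might also infer shifts of tens of points in both directions. The table does not show that: the largest upward shift is 11 points, and at CV 0.5 the shifts are −7/+8 (mean 500) and −11/+5 (mean 1500).

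Finally, the class results are additional to the overall CR and ERR, no decision rule is attached to them, the two-group comparison is optional, and a SAP not shown may set the class limits. This limits the consequence. It does not remove the bias, because the protocol itself fixes both the stratification and the single baseline count.

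**Conclusion.** The point holds as a conditional caution about ERR by baseline class. The direction follows from the design: with one baseline count used both for classing and as T1, the ERR is pushed down in the lightest class and up in the heaviest. The amount is unknown because the protocol gives no sample-to-sample CV. It runs from about 1 point (counting error only) through 2-3 points (CV 0.25) and 7-11 points (CV 0.5) to 12-24 points (CV 0.71) in an illustrative 150-499 epg class at a true 80%. At a true 95% and CV 0.5 it is 2-3 points.

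The overall ERR of sample means is largely unaffected, so this does not undermine the main efficacy estimate. Whether areas with different drug exposure differ in intensity is not stated; if they do, within-class comparisons between them are exposed to the same artefact. The figures concern ERR. Class-specific CR has a different distortion and is not quantified here.

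**What to change.** Add to Data analysis: ERRs by class of T1 are descriptive; neither a gradient across classes nor a difference between areas within a class will be interpreted as density dependence or as reduced efficacy.

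If density dependence is to be assessed, use a paired-count model with a child-level latent intensity that allows for counting error, sample-to-sample variation and between-child variation in response. Report it over an assumed range of sample-to-sample CV, because one count before and one after treatment cannot separate these sources.

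Do not class children by an average that includes T2, such as the mean of T1 and T2/(1 − overall ERR). It looks attractive when every child has the same reduction, but it lets the outcome decide the class. With response varying between children independently of intensity (remaining fraction Beta(2,8), mean reduction 80%; intensity mean 500, CV 0.5), such classes read about 89-83-80-76-66%, a false decline of 23 points. At 95% efficacy one residual egg scales to 50/0.05 = 1000 epg, so a child with T1 = 150 averages (150 + 1000)/2 = 575 epg. The 150-499 class then contains only egg-free children and reads 100% by construction.

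Cost: one sentence, a little more analysis if the model is wanted, and a weaker statement about density dependence. No new data are needed.

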### Sample size

The initial number of schoolchildren to sample will depend on the prevalence of the STH in the study region as a minimum of 250 infected children with a minimum of 150 eggs/gram of any species of STH (i.e. *Ascaris* or hookworms or *Trichuris*) should be recruited at each study site e.g. with an expected prevalence of 50% for any specific STH 500 schoolchildren should be enrolled in the first sampling.

If the epidemiological scenario allows, individual study sites may include two groups of children (each with 250 infected children with a minimum of 150 eggs/gram of any species of STH): (1) a group of children resident in areas where the government had, for  $\geq$  than 3 years, a regular (one or two treatments/year) mass drug administration program with a benzimidazole anthelmintic (albendazole or mebendazole) and (2) a group of children resident in areas where there is no mass drug administration program.

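### The allowance for 25% loss is taken as 200 × 1.25 = 250 when it needs 200/0.75 = 267, and the 500-child screening example leaves out the 150 eggs/gram threshold

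*Protocol*

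**What the plan says.** Footnote 1, attached to Sample size and printed under Data analysis in the protocol, gives two bases for the number of children, at alpha 0.05 and 80% power.

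- Simulated egg-count data: "a sample size of up to 200 individuals" is needed to detect a "10 percentage point drop from a null efficacy of" about 80%.
- Cure rate, by standard methods for proportions: "sample sizes ranging up to 200 (the largest samples being required to detect departures from null efficacies around 50" per cent.

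It then allows for loss: "Given an anticipated non-compliance rate of 25%, a sample of 250 individuals with" more than 250 eggs per gram before treatment "should therefore be followed up for post-treatment FEC data at each study locality".

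The Sample size section uses the same number as a recruitment target: "a minimum of 250 infected children" "with a minimum of 150 eggs/gram of any species of STH" at each site. Its example of the first sampling is: "with an expected prevalence of 50% for any specific STH 500 schoolchildren should be enrolled in the first sampling". Where a site studies two groups, each group has the same target of 250.

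Two other sections matter here. Experimental design restricts the second sampling to children at 150 eggs/gram or more. The section on the parasitological technique, with Annex 2.1, gives one-chamber McMaster a detection limit of 50 eggs/gram, with counts in multiples of 50.

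**The concern.** The plan has two steps from the power calculation to the number of children screened, and each has an arithmetic slip.

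The first is the loss allowance. When a quarter of recruited children are expected to give no usable follow-up, the evaluable number must be divided by 0.75. Multiplying it by 1.25 leaves too few.

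The second is the screening example. Infection is detectable from 50 eggs/gram, but a child counts toward the 250 only from 150. Dividing 250 by the prevalence of infection treats every infected child as eligible.

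At stake are a power statement that does not match the numbers behind it and a worked example that understates the screening load. The example matters because the overall objective is a standard monitoring protocol, so other sites may copy it.

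**Working it through.** **Inputs.** From footnote 1: up to 200 evaluable, alpha 0.05, power 80%, a 10-point drop, 25% non-compliance. From Sample size: 250 children at 150 eggs/gram or more, 50% prevalence, 500 screened. The footnote states neither the sidedness nor the test. I assume a two-sided, one-sample comparison with a fixed null rate, because that reproduces the plan's figure.

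**The plan's 200.** With p0 = 0.50 and p1 = 0.40:

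n = [1.96·√(0.5·0.5) + 0.8416·√(0.4·0.6)]² / 0.10² = 193.8, so 194.

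With continuity correction it is 204. A one-sided test would need 153. The stated upper figure of 200 is therefore reproduced on the two-sided assumption.

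**The plan's 250.**
- 200 × (1 + 0.25) = 250, which is the stated figure.
- 200 / (1 − 0.25) = 266.7, so 267, which is the number that leaves 200.
- 250 × 0.75 = 187.5, so about 187 evaluable. 250 leaves 200 only if loss is 1 − 200/250 = 20%.

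**Power at 187** (normal approximation): Φ{[|p0 − p1|·√n − 1.96·√(p0(1−p0))] / √(p1(1−p1))}.

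| Null vs alternative | n = 187 | n = 200 |
|---|---|---|
| 50% vs 40% | 78.6% | 81.2% |
| 80% vs 70% | 89.9% | 91.6% |
| 90% vs 80% | 97.4% | 98.1% |

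The detectable drop at 187 is about 10.2 points. For 50% against 39.8%, n = [1.96·0.5 + 0.8416·√(0.398·0.602)]² / 0.102² ≈ 186.

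The egg-count simulation cannot be rerun from the document. If 200 gave exactly 80% power there, a normal approximation puts 187 at Φ(2.80·√(187/200) − 1.96), about 77%.

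**The plan's 500.** 250 / 0.50 = 500, which is the stated figure. No factor for intensity enters. With one chamber, one or two eggs counted means 50 or 100 eggs/gram: positive, but below 150.

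Let f be the share of infected children at or above 150 eggs/gram. The documents do not give f, so the values below are assumptions. Number to screen = target / (0.50·f).

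| f | Screened for 250 | Screened for 267 | Eligible if a site stops at 500 | Left after 25% loss |
|---|---|---|---|---|
| 1.0 | 500 | 534 | 250 | 187 |
| 0.9 | 556 | 594 | 225 | 169 |
| 0.8 | 625 | 668 | 200 | 150 |
| 0.7 | 715 | 763 | 175 | 131 |
| 0.5 | 1000 | 1068 | 125 | 94 |

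The example is right only at f = 1, or if prevalence is meant as prevalence at or above the threshold, which the text does not say.

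**The case against.** **The 250 may be children who complete follow-up.** The footnote does say that 250 should be followed up, and 250 completers would exceed 200. But it derives the 250 from the 25% non-compliance, and Sample size sets the same 250 as the number recruited. Followed up can also simply mean targeted for the second sampling. What remains is a wording ambiguity, and it does not rescue the arithmetic.

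**The loss allowance costs little.** This stands. The 200 is an upper figure, reached only near a 50% cure rate, and the drop is stated only as about 10 points.

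**Exact binomial power looks worse.** A reader might infer a larger shortfall from exact power of 75.9% at 187. Exact power moves in a sawtooth: it is 78.5% at 188, and only 78.7% at the plan's own 200. Setting an exact figure against a target derived by normal approximation exaggerates the loss.

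**The 500 is only an example.** This also stands. The operative rule is a minimum of 250 eligible children, and the initial number is said to depend on prevalence. A site that finds too few among 500 has not met the minimum.

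**Co-endemic species help.** The 50% refers to any specific STH, while eligibility is by any species. Where several species circulate, more children qualify than one species' prevalence suggests, which offsets part of the gap.

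**Conclusion.** Both slips are in the text.

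The loss allowance gives 250 where 267 is needed, leaving about 187 evaluable, some 6% below 200. In the footnote's worst case this costs under 3 points of power (78.6% against 81.2%), assuming a two-sided one-sample test. Near 80% efficacy, treated as a proportion, power stays about 90%.

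The screening example is too low by a factor 1/f. The size of that cannot be fixed from the documents; the assumed range of 0.9 to 0.5 gives 556 to 1000 screened instead of 500, before any offset from co-endemic species.

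A reader might infer that sites will run with seriously reduced power. With f = 0.8, for instance, stopping at 500 would leave 150 evaluable and about 69% power for 50% against 40%. The documents do not support that as a consequence of the plan. It needs an assumed f, and it treats the illustration as a cap although 250 eligible children is the stated minimum. This is mainly a screening-number error, with a power loss beyond the first step only where a site stops at 500.

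One related inconsistency bears on the screening number. The footnote attaches more than 250 egg/g to the 250 children, while Sample size and Experimental design use 150 eggs/gram. A higher threshold would lower f further.

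**What to change.** 1. Either keep 250 recruited and state that 25% loss leaves about 187 evaluable, with about 79% power for 10 points near a 50% cure rate (or 80% power for about 10.2 points), or state 267 recruited. Apply the choice to each group where a site studies two.
2. Use one term for the 250, recruited or followed up, in both the footnote and Sample size.
3. Replace the example by a formula: first-sampling N = target / expected prevalence of infection at or above the eligibility threshold in any STH species. This keeps eligibility by any species.
4. Reconcile the footnote's >250 egg/g with the 150 eggs/gram in Sample size and Experimental design.

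Keeping 250 costs only restated text. Choosing 267 adds 17 eligible children per site or group. The corrected formula gives sites with many light infections a larger screening number, a workload that the minimum of 250 eligible children already implies.
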